### Study measures

3.5

An overview of all study measures can be found in Table 1. All questionnaires will be employed online via REDcap. They will be used in German, English, Turkish, Persian, Ukrainian and Arabic. Questionnaires that are not yet available in these languages will be translated using the Multiple-Forward-Approach.

**Table 1 tab1:** Assessment summary.

	Screening (t0)	Baseline (t1)	Post-intervention (t2)	Follow-up (t3)
Sociodemographic data	x			
Screening instruments				
K-10	x			
SBQ-R	x			
WHO-5	x			
Primary outcome				
HSCL-25	x	x	x	x
Secondary outcomes				
PSS-10		x	x	x
CYRM-R		x	x	x
ER-40		x	x	x
Other measures				
RPMS		x		
LEC-5		x		
CSQ-8			x	x

The table shows a summary of all study assessments.

#### Screening measures

3.5.1

Screening measures include demographics such as age or country of origin, inclusion criteria including the HSCL-25 and the K10, exclusion criteria including the SBQ-R, and the World Health Organization Well-Being Index (WHO-5).

The K10 is a 10-item self-report questionnaire aimed at assessing overall distress levels. It gathers information on anxiety and depressive symptoms experienced by an individual within the past 4 weeks. Participants answer on a 5-point Likert Scale (1 = none of the time, 5 = all of the time), with scores ranging from 10 to 50. Higher scores indicate a higher possibility that participants suffer from a mental disorder.

The SBQ-R is a brief, 4-item self-report measure of past suicidal behavior. The questionnaire is used with adolescents between the ages of 13 and 18. Each question is rated on its own scale, with specific point values assigned to the answers and the total score ranging from 3 to 18 points. A higher score indicates a greater likelihood of engaging in suicidal behavior.

The WHO-5 is a brief self-report assessment used to measure mental well-being during the past 2 weeks. It includes five items with positive wording, each rated on a 6-point Likert scale (0 = at no time, 5 = all of the time). The total raw score, which ranges from 0 to 25, is multiplied by 4 to generate the final score. A high score indicates a higher level of well-being.

#### Primary outcome

3.5.2

The primary outcome, symptoms of depression and anxiety, will be measured by the HSCL-25 (36) at baseline (t1), at the end of the intervention (t2) and 12 weeks after the end of the intervention (t3) to determine the effectiveness of the intervention. The HSCL-25 is a 25-item self-report questionnaire, on which participants rate if physical, emotional, or psychological symptoms indicating depression, anxiety, and trauma have affected them over the past week. Answers are given on a 4-point Likert Scale (1 = not at all; 4 = extremely), and total scores can range from 25 to 100, with higher scores indicating greater levels of depression, anxiety and trauma, respectively.

#### Secondary outcomes

3.5.3

The secondary objective perceived stress will be measured by the PSS-10 (54) at baseline (t1), at the end of the intervention (t2) and 12 weeks after the end of the intervention (t3). The PSS-10 is a 10-item self-report questionnaire including two subscales, on which participants report life as unpredictable, uncontrollable, and overloading over the previous month. Answers are given on a 5-point Likert Scale (0 = never, 4 = very often). Higher scores indicate higher levels of perceived stress.

The secondary objective social-ecological resilience will be measured by the CYRM-R (55) at baseline (t1), at the end of the intervention (t2) and 12 weeks after the end of the intervention (t3). The CYRM-R is a 17-item self-report questionnaire measuring resilience that has been validated in 11 different countries (55). Items include social integration and support, autonomy and fair treatment and can be answered on a 3- point Likert Scale (1 = no, 3 = yes). Higher scores indicate more available protective factors and higher social-ecological resilience.

The secondary objective facial emotion recognition will be measured using the ER-40 (56) at baseline (t1), at the end of the intervention (t2) and 12 weeks after the end of the intervention (t3). The ER-40 consists of 40 color photographs of static multicultural faces expressing four basic emotions (i.e., happiness, sadness, anger or fear) and neutral expressions. Participants quickly select the appropriate emotion label for each face. They then rate their confidence in the accuracy of their response on a scale from 0 (not at all confident) to 100 (extremely confident). Accuracy scores range from 0 to 40. The ER-40 has strong psychometric properties and is recommended for use in clinical trials (57).

#### Other measures

3.5.4

The Refugee Post-Migration Stress Scale (RPMS) (58) is a self-report questionnaire consisting of 21 items that assess various stressors experienced by refugees after migrating to a new country and will be measured at baseline (t1). The scale was originally developed for migration to Sweden and adapted to the Swiss context. Participants rate how often they have experienced each stressor after resettlement in Switzerland on a 5-point Likert Scale (1 = never; 5 = always). Total scores on the RPMS can range from 21 to 105, with higher scores indicating higher levels of post-migration stress.

The Life Events Checklist for DSM-5 (LEC-5) will be employed at baseline (t1) as a self-report questionnaire used to assess exposure to events that could potentially cause post-traumatic stress disorder (PTSD), depression, or distress. Participants indicate varying levels of exposure to each type of potentially traumatic event included on a 6-point Likert Scale (1 = does not apply, 6 = happened to me). The LEC-5 does not provide a total or composite score.

To assess the strengths and weaknesses of the intervention, participants will fill out the Client Satisfaction Questionnaire (CSQ-8) at the end of the intervention (t2). The CSQ-8 is a self-report questionnaire used to assess client satisfaction with services received. It consists of 8 items that measure various aspects of satisfaction, such as the perceived helpfulness of the service, the extent to which the client’s needs were met, and overall satisfaction with the care received. Each item is rated on a 4-point Likert Scale.

## Statistics

4

### Sample size

4.1

The sample size is estimated based on a power analysis for repeated measures ANOVA including within-between interaction with 3 measuring time-points (t1, t2 and t3) and 2*2 groups (intervention vs. TAU, female vs. male). Standard parameters are set at alpha = 0.05, power = 0.95, and a clinically meaningful medium effect size *f* = 0.25. Considering an attrition rate of 30% (59), the total number of participants should be 80, with approximately 40 participants in the treatment (treatment groups of 5 to 10 participants each) and 40 participants in the control group.

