### Statistical analyses

4.2

For statistical analyses, we will use R with its graphical user interface R Studio. The significance level will be 0.05 for all analyses. An effect of at least moderate size will be considered as clinically relevant. To test our hypotheses, we will use multilevel models with primary and secondary outcome measures as dependent variables (three individual models for depression, perceived stress, and emotion recognition), and with timepoint (baseline, post-treatment, follow-up) and intervention condition (START NOW vs. TAU) including their interaction as independent variables. A significant interaction between intervention condition and time suggests a difference in symptom change depending on treatment group. In case of significant main or interaction effects, we will evaluate post-hoc contrast considering time and intervention condition. Treatment group will be added as level two in the multilevel framework.

Using multilevel models will allow to analyze data on the observational level, which provides more information in contrast to calculating change scores or using repeated measures ANOVA, increasing measurement accuracy and power. In addition, multilevel mixed models can handle missing observations and allow to examine random effects at the intercept and slope level. Furthermore, we will test model improvement when considering quadratic versus linear trends for time, random effects for time, and correlation structure between timepoints. Covariates, including participant age, gender, and post-migration stress will be added if they differ between intervention groups. On group level, possible covariates include facilitator, institution or cultural background.

To analyze perceived stress and resilience as potential mechanisms in treatment success, we will use bias-corrected bootstrap mediation models with intervention condition as predictor, change in symptoms of depression as outcome, and change in stress/resilience as mediator. Change in symptoms of depression and indicators of stress/resilience will consist of participant’s random slope for time extracted from the multilevel mixed models depending on results of the first hypothesis.

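### Section 4.1 claims 0.95 power for a medium effect, but f = 0.25 in the interaction it sizes is an arm difference of about 1.06 SD; power for 0.5 SD is well below 0.95

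*Protocol article*

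**What the plan says.** The Sample size section (4.1) bases the number on a "power analysis for repeated measures ANOVA including within-between interaction". The layout is "3 measuring time-points (t1, t2 and t3) and 2*2 groups (intervention vs. TAU, female vs. male"). The inputs are given as follows: "Standard parameters are set at alpha = 0.05, power = 0.95, and a clinically meaningful medium effect size", namely f = 0.25. The total follows: "Considering an attrition rate of 30% (59), the total number of participants should be 80", about 40 per arm, with the intervention delivered in groups of 5 to 10. No correlation between time points is given.

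The Statistical analyses section (4.2) tests the hypotheses with multilevel models containing time, intervention condition and their interaction. Gender enters only as a covariate, and only if it differs between arms. Treatment group forms level two. The section adds: "An effect of at least moderate size will be considered as clinically relevant". It does not say on which scale moderate is measured.

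**The concern.** There are two difficulties. The main one is the label on the effect size. In a plain comparison of two means f = d/2, so f = 0.25 corresponds to d = 0.5. In a group-by-time interaction f measures something else, and the same 0.25 stands for a much larger difference between arms. The second is that the sizing has four groups, while the analysis compares two arms.

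The trial calls itself confirmatory and makes a moderate effect its threshold for clinical relevance. A reader who accepts 0.95 power for a medium effect would take a non-significant result as strong evidence against a moderate benefit. If the power for such a benefit is much lower, that inference fails.

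**Working it through.** **Inputs from section 4.1:** k = 4 groups, m = 3 time points, alpha 0.05, power 0.95, f = 0.25, 30% attrition, N = 80, hence 80 × 0.7 = 56 completers. **Assumed:** the correlation rho between time points (0.5, with 0.3 to 0.7 as the range), and d = 0.5 SD as the meaning of moderate.

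**1. Reproducing the plan's figure.** For the within-between interaction, use a noncentral F with lambda = f²·N·m/(1 − rho), df1 = (k − 1)(m − 1) and df2 = (N − k)(m − 1).

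- rho = 0.5, N = 60: lambda = 0.0625 × 60 × 3/0.5 = 22.5, df 6 and 112, power 0.954.
- rho = 0.5, N = 56: lambda = 21.0, df 6 and 104, power 0.937.
- rho = 0.53, N = 56: lambda = 22.3, power 0.952. For rho from 0.53 to 0.56 the smallest N in four equal groups is 56, and 56/0.7 = 80.

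So the stated 80 is recovered with this formula. The other effect-size conventions, which lack the rho adjustment, need 172 to 176 completers for four groups and cannot give 80.

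**2. What f = 0.25 means as an arm difference.** With arm differences delta_t at the three time points, f² is the mean over time of ((delta_t − mean delta)/2)². If the arm effect is the same in both genders, f is the same for the two-arm and four-group layouts.

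- Sustained effect (0, d, d): the mean is 2d/3 and the halved deviations are −d/3, d/6, d/6. Then f² = (1/9 + 1/36 + 1/36)d²/3 = d²/18, and f = 0.25 gives d = 0.25 × √18 = 1.06 SD.
- Linear build-up (0, d/2, d): f² = (1/16 + 0 + 1/16)d²/3 = d²/24, and d = 0.25 × √24 = 1.22 SD.
- In reverse, d = 0.5 sustained is f = 0.5/√18 = 0.118.

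This conversion does not involve rho.

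**3. Power of the planned test at d = 0.5, sustained.** Two arms with time as three levels give df1 = 2 and df2 = 2(N − 2). Example: N = 56, rho = 0.5, f² = 0.25/18, so lambda = (0.25/18) × 56 × 3/0.5 = 4.67 and power is 0.464 (simulation: 0.466).

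| rho | 56 analysed | 80 analysed |
|---|---|---|
| 0.3 | 0.345 | 0.475 |
| 0.5 | 0.464 | 0.624 |
| 0.7 | 0.692 | 0.849 |

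With a linear build-up to 0.5 SD at rho = 0.5, power is 0.36 with 56 and 0.50 with 80.

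**4. Does the four-group layout cause this?** At f = 0.25, rho = 0.5 and 56 completers, the two-arm test has power 0.987 against 0.937 for four groups. It does not.

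**5. Larger differences, two-arm test, 56 completers, rho = 0.5:** 0.7 SD gives lambda = 9.15 and power 0.77; 0.75 SD gives lambda = 10.5 and power 0.82.

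None of these figures includes clustering.

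**The case against.** The best defence is that the protocol defines its medium effect as f = 0.25 and never mentions d = 0.5. On its own scale the calculation is about right, and the two-arm test would have even more power. That stands as a description of the arithmetic. It does not rescue the label, because f = 0.25 here is a difference of a full standard deviation or more.

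Second, 56 is a floor on the data used. The multilevel model keeps partial records, so the information lies between 56 and 80 complete cases. This stands, and is why both columns are shown. A correlation of 0.8 would give 0.86 with 56 and 0.96 with all 80, but the stated 80 is reproduced only at rho near 0.5 to 0.56. A baseline-adjusted average of t2 and t3 would reach about 0.74 with 56 at rho = 0.5; that is not the test section 4.2 names, and it is still short of 0.95.

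Some stronger readings are tempting but not supported:

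- A reader might infer that attrition was inflated wrongly, because at rho = 0.5 the need is 60, 60 × 1.3 = 78 is close to 80, and 60/0.7 = 86. The section gives neither the uninflated number nor rho, and 56/0.7 = 80 is correct inflation at rho of about 0.53 to 0.56.
- A reader might blame the arm-by-gender layout for the low power. Step 4 shows otherwise.
- A reader might take 46% as the trial's power. It is one point in a range that depends on unstated inputs.
- A reader might say the relevance rule adds nothing beyond significance. That holds only if moderate is fixed at about 0.5 SD, which the protocol does not do.
- Clustering in groups of 5 to 10 would lower power further, but no intracluster correlation is given, so no size can be attached. The analysis itself does model treatment group.

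**Conclusion.** The power statement is wrong as written. Section 4.1 attaches 0.95 power to an effect it calls medium, when the calculation behind N = 80 is for an arm difference of 1.06 SD (sustained) or 1.22 SD (linear build-up). That part rests only on the formula that reproduces the stated N and on the shape of the effect over time.

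The size of the shortfall rests on more: moderate read as 0.5 SD, a sustained effect, time as three levels, and rho. Under these, power is 0.35 to 0.69 with 56 analysed and 0.48 to 0.85 with 80, for rho from 0.3 to 0.7. Every value is below 0.95 before clustering.

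The mismatch between a 6-df arm-by-gender-by-time sizing and a 2-df condition-by-time analysis is a real inconsistency to be reconciled, but it costs no power at the stated f.

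**What to change.** Keep N = 80. Rewrite section 4.1 for the two-arm condition-by-time test of section 4.2, stating the assumed correlation, the number analysed, the shape of the effect over time and the effect in HSCL-25 SD units. For example, with 56 completers, rho = 0.5 and a sustained effect, before clustering: power about 0.46 for 0.5 SD, 0.77 for 0.7 SD and 0.82 for 0.75 SD. Note that clustering in treatment groups lowers these figures.

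Remove the claim of 0.95 power for a medium effect. In section 4.2, say which scale and value the moderate threshold refers to, and commit to reporting the standardised arm difference with its confidence interval, so that a null result is not read as excluding a moderate benefit.

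The cost is one rewritten paragraph, one added sentence and a less favourable stated power. No participants are added, and neither the conduct of the trial nor the planned test changes.

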### Statistical analyses

4.2

For statistical analyses, we will use R with its graphical user interface R Studio. The significance level will be 0.05 for all analyses. An effect of at least moderate size will be considered as clinically relevant. To test our hypotheses, we will use multilevel models with primary and secondary outcome measures as dependent variables (three individual models for depression, perceived stress, and emotion recognition), and with timepoint (baseline, post-treatment, follow-up) and intervention condition (START NOW vs. TAU) including their interaction as independent variables. A significant interaction between intervention condition and time suggests a difference in symptom change depending on treatment group. In case of significant main or interaction effects, we will evaluate post-hoc contrast considering time and intervention condition. Treatment group will be added as level two in the multilevel framework.

Using multilevel models will allow to analyze data on the observational level, which provides more information in contrast to calculating change scores or using repeated measures ANOVA, increasing measurement accuracy and power. In addition, multilevel mixed models can handle missing observations and allow to examine random effects at the intercept and slope level. Furthermore, we will test model improvement when considering quadratic versus linear trends for time, random effects for time, and correlation structure between timepoints. Covariates, including participant age, gender, and post-migration stress will be added if they differ between intervention groups. On group level, possible covariates include facilitator, institution or cultural background.

To analyze perceived stress and resilience as potential mechanisms in treatment success, we will use bias-corrected bootstrap mediation models with intervention condition as predictor, change in symptoms of depression as outcome, and change in stress/resilience as mediator. Change in symptoms of depression and indicators of stress/resilience will consist of participant’s random slope for time extracted from the multilevel mixed models depending on results of the first hypothesis.

The qualitative interviews will apply an inductive approach and follow empirical guidelines as suggested by Mayring (60). The aim is to conduct an estimate of five to eight interviews across different institutions, each of around 30 min in length. After recording (audio), the interviews will be transcribed and the audio files will be destroyed. Pertaining to the inductive categorization, evaluation and illustration of the qualitative data, MAXQDA will be employed (61).

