### Hypotheses

2.2

Based on our primary and secondary endpoints, we have formulated the following hypotheses.

START NOW Adapted will be more effective than TAU in reducing symptoms of depression and anxiety, as assessed by the Hopkins Symptom Checklist (HSCL-25).START NOW Adapted will be more effective than TAU in reducing perceived stress, as assessed by the Perceived Stress Scale (PSS-10).START NOW Adapted will be more effective than TAU in increasing social-ecological resilience, as assessed by the Child and Youth Resilience Measure (CYRM-R).START NOW Adapted will be more effective than TAU in increasing facial emotion recognition, as assessed by the Penn Emotion Recognition Task (ER-40).

Additionally, besides investigating the intervention’s effectiveness, we aim to examine potential mediators to uncover the mechanisms of action (28). Specifically, we hypothesize:

The relationship between the group condition and changes in depressive and anxious symptoms (HSCL-25) is mediated by stress reduction (PSS-10).The relationship between the group condition and changes in depressive and anxious symptoms (HSCL-25) is mediated by increased resilience (CYRM-R).The relationship between increased resilience (CYRM-R) and changes in depressive and anxious symptoms (HSCL-25) is mediated by stress reduction (PSS-10).

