### Study design

3.1

The study is a confirmatory, randomized controlled trial with two arms that takes place in a monocentric, national setting and assesses effectiveness.

To evaluate feasibility, qualitative semi-structured interviews will be conducted with specialists working with refugees prior to the intervention study. These interviews will follow an inductive and explorative approach and involve staff from institutions such as asylum centers and dormitories for unaccompanied minors. To estimate the feasibility and effectiveness of this trial, specialists will be interviewed about their daily challenges, language and cultural barriers, as well as potential difficulties with the implementation and adaptation of START NOW. The inclusion of qualitative information can help to better understand how a complex intervention such as START NOW can work and aid in the adaptation process of the intervention (31).

After the conduction of these interviews, possible participants taking part in the intervention study are screened for eligibility. For those who are eligible, the study duration will be 6 months, including three assessments (shown in Figure 1): a baseline assessment (t1), a post-treatment assessment (t2), and a 12-weeks follow-up assessment (t3). In case a participant has missed a session, they will be marked as absent and the number of sessions will be taken into consideration in the data analysis. To minimize bias, participants will be randomly assigned to one of two experimental group conditions, (1) group skills training using an adapted version of START NOW, (2) TAU. Randomization should take place within 2 weeks before the intervention, after the baseline assessment (t1) has been conducted. Between t1 and t2, the intervention phase takes place over a period of 10 weeks, with one session per week for each group. The study takes place in a group setting since conducting mental health interventions via group workshops, which aim to enhance social interaction was observed to have a positive impact on participants’ mental health (19). For ethical reasons and to increase study-related commitment, participants in the control group (receiving TAU) as well as non-eligible participants will be offered the chance to receive treatment after the study concludes.

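### Unadjusted arm contrasts may follow any significant main effect and the shape of time is chosen from the data, so the confirmatory HSCL-25 test is not fixed and can exceed 5%

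*Protocol article*

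**What the plan says.** Study design in the protocol article sets the standard: "The study is a confirmatory, randomized controlled trial with two arms". Sample size bases the number of participants on a "repeated measures ANOVA including within-between interaction with 3 measuring time-points (t1, t2 and t3) and 2*2 groups".

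Statistical analyses then fixes four rules:

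- On the level: "The significance level will be 0.05 for all analyses". No adjustment is stated.
- On reading the result: "A significant interaction between intervention condition and time suggests a difference in symptom change depending on treatment group". The interaction is not named as the only criterion of success.
- On follow-up tests: "In case of significant main or interaction effects, we will evaluate post-hoc contrast considering time and intervention condition".
- On the form of time: "we will test model improvement when considering quadratic versus linear trends for time, random effects for time, and correlation structure between timepoints".

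Primary outcome gives this schedule for HSCL-25: "at baseline (t1), at the end of the intervention (t2) and 12 weeks after the end of the intervention (t3) to determine the effectiveness". No time point has priority. The first item under Hypotheses names no time point either.

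**The concern.** A gate protects the tests behind it only if it rarely opens when there is no treatment effect. The main effect of time does not have that property. It asks whether the average of both arms changes, and it can be large when the arms are identical.

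Such a change is plausible here. Eligibility criteria require HSCL-25 above 1.75 or K10 above 20, so some regression to the mean is likely, and symptoms may also improve under usual care. HSCL-25 is measured again at baseline after screening, so part of the regression may be over before t1. The size of any common shift is therefore unknown.

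If it occurs, the written rule opens arm contrasts at t2 and t3, each at 0.05, even when the interaction is not significant. Separately, the interaction test takes its form from a comparison made on the same data. At stake is whether a positive HSCL-25 result can be called confirmatory at 5%.

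**Working it through.** **Inputs from the article.** Alpha 0.05, power 0.95, f = 0.25, three time points, 2 × 2 groups, 30% attrition, total 80 (Sample size). Completers: 80 × 0.70 = 56, or 28 per arm.

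**Assumptions, since the article gives no figure.** Two-sided tests; equal correlation ρ = 0.3, 0.5 or 0.7 between occasions; a shift common to both arms of 0, 0.2 or 0.5 SD at t2 and t3; 28 or 40 per arm. Dropout patterns, clustering by treatment group and covariate choice are left out.

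**Step 1. Reproduce the sample size.** For a within-between interaction with k groups and m occasions, λ = f²·N·m/(1 − ρ), df1 = (k − 1)(m − 1) and df2 = (N − k)(m − 1). With k = 4, m = 3, ρ = 0.5 and N = 60:

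- λ = 0.0625 × 60 × 3/0.5 = 22.5
- df1 = 6, df2 = 112
- N = 60 is the smallest balanced total with power of at least 0.95
- 60 × 1.30 = 78, close to the stated 80

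So the number of participants rests on a test of group by time with time as three occasions. The arm-by-time test is a 2-df part of it.

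**Step 2. Two arm contrasts with no gate.** For two independent tests the bound is 1 − 0.95² = 9.75%. The changes t2 − t1 and t3 − t1 share the baseline. Each has variance 2(1 − ρ) and their covariance is 1 − ρ, so they correlate at 0.5 whatever ρ is. Their joint error is therefore a little below 9.75%.

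**Step 3. The rule as written.** The contrasts are examined if arm, time or interaction is significant at 0.05. A false claim is a significant arm difference in change to t2 or to t3 when there is no arm effect. Ranges are over ρ = 0.3 to 0.7.

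| Common shift | Gate opens (40 per arm) | False claim, 28 per arm | False claim, 40 per arm |
|---|---|---|---|
| 0 | about 14% | 4.6-4.9% | 4.5-4.8% |
| 0.2 SD | 39-68% | 5.3-6.6% | 5.9-7.5% |
| 0.5 SD | 98-100% | 8.7-9.1% | 8.6-9.0% |

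At 0.5 SD and 28 per arm the gate opens in at least 91% of null trials. It then gives almost no protection, and the error approaches the ungated value of Step 2.

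**Step 4. Trend chosen from the data.** Quadratic time is kept if its terms are significant at 5%; the interaction in the chosen model is then tested jointly. Type I error is 5.5-6.9%.

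**Step 5. After the repair.** The 2-df arm-by-time interaction with time as a factor gives 4.8-5.1%. If the t2 and t3 contrasts open only after that interaction is significant, a false claim occurs in 4.0-4.3%.

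**The case against.** The strongest reply is that a narrower reading exists. The trial is sized on the interaction, and only the interaction is explained as a treatment-related difference in change. The follow-up contrasts are labelled post hoc, and after a time main effect they could be contrasts between occasions only. On that reading the confirmatory test is the interaction. With time as a factor it holds 5% and needs no primary time point. This stands as a possible reading, and timepoint is indeed listed by its three occasions. But the sentence names main effects and intervention condition together, the interaction is not made the sole criterion, and the next paragraph leaves the form of time open. These are rules that the article itself sets, so they are not simply detail left to an analysis plan.

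The size of the problem is also open to challenge, and rightly. With no common time shift there is no inflation from the gate, and trend selection adds at most about two percentage points under a joint test.

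Three stronger readings are tempting but unsupported:

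- *That the plan could miss an end-of-treatment effect that fades by t3.* For an effect pattern (0, −d, 0), the linear contrast (−1, 0, 1) does give zero, but the quadratic contrast (1, −2, 1) gives 2d. The plan's own comparison picks this up. With 28 per arm and ρ = 0.5, power after selection is about 46% at d = 0.5 and 98.7% at d = 1.06, the same as with categorical time.
- *That error should be pooled over all outcomes.* Perceived stress, resilience and emotion recognition are declared secondary. They do not decide the primary hypothesis, and their ordering or adjustment is ordinary analysis-plan content.
- *That any single significant interaction term counts as success.* That would raise the trend-selection error to 7.3-9.6%, but the article does not say so.

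**Conclusion.** The point holds in limited form. As written, the article does not tie the confirmatory HSCL-25 claim to one fixed test, and one of its routes to an arm contrast passes through an effect that says nothing about the arms. The false-claim rate runs from the nominal level with no common time shift to about 9% with a shift of 0.5 SD. It depends on that shift and on the correlation, neither of which the article gives, and on reading the rule as allowing arm contrasts after a time main effect. Trend selection is the smaller contributor, at about 5.5-7% by itself. The documents do not show that the error must exceed 5%, nor that a real effect would be lost. Correcting the wording is worthwhile because the trial is presented as confirmatory and the correction is cheap.

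**What to change.** In Statistical analyses:

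1. State that the single confirmatory test is the arm-by-time interaction on HSCL-25 total, two-sided at 0.05, with time as a three-level factor fixed in advance. This is the kind of test used for the sample size. With three occasions, linear plus quadratic time already reproduces a three-level factor, so no shape of change is given up.
2. Strike the words *main or* from the sentence on contrasts, so that arm contrasts at t2 and t3 follow only a significant interaction.
3. Label linear and quadratic trend modelling as exploratory.

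An acceptable alternative is to name one arm contrast on HSCL-25 at one time point as the primary test, at 0.05 and not gated by any other test. The two options should not be combined, since gating a primary contrast on the interaction would make it conditional. Which option, and which time point under the second, is for the sponsor to choose.

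The cost is wording and the freedom to choose the growth shape after seeing the data. No participants, visits or measures are added.
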